## Abstract

**Background:**

Incisional hernia is the most common long-term complication after abdominal surgery, including minimally invasive colorectal procedures. In Japan, fascial closure of small midline incisions is generally performed using interrupted suturing, but high-quality evidence comparing continuous barbed suturing with interrupted suturing is limited. Continuous closure may reduce the risk of incisional hernia; however, robust randomized data in laparoscopic and robot-assisted colorectal surgery are lacking. This study aims to determine whether continuous barbed suturing is superior to conventional interrupted suturing in preventing incisional hernia after minimally invasive colorectal cancer surgery.

**Methods:**

The HIBISCUS trial is a multicenter, prospective, open-label, randomized controlled study comparing continuous barbed suturing with interrupted monofilament suturing for fascial closure of mini-laparotomy incisions. Eligible adults with colorectal cancer undergoing elective laparoscopic or robot-assisted resection will be randomized 1:1 to continuous closure using a barbed absorbable suture (STRATAFIX Symmetric PDS Plus; bite width of 5 mm and stitch spacing of 5 mm) or interrupted closure using a monofilament absorbable suture (PDS Plus; bite width of 8 mm and stitch spacing of 8 mm). Only board-certified surgeons who complete a standardized pre-trial suturing competency assessment will be allowed to participate. The primary endpoint is the incidence of incisional hernia within 18 months after surgery, assessed mainly by scheduled abdominal CT imaging, with clinical examination as complementary. Secondary endpoints include fascial closure time, postoperative wound complications (including surgical site infection (SSI)), postoperative wound pain, and reoperation or readmission. All CT images will be independently reviewed by two blinded specialists. Based on power calculations, 422 patients will be enrolled.

**Discussion:**

This trial will be the first randomized study to directly compare continuous barbed suturing with conventional interrupted suturing for small midline incisions in minimally invasive colorectal surgery. By standardizing suturing parameters and requiring surgeon competency verification, the HIBISCUS trial is designed to yield high-quality evidence on optimal fascial closure technique. The results are expected to influence clinical practice, inform guideline development, and contribute to the global standardization of abdominal wall closure practices.

**Trial registration:**

This study is registered in the Japan Registry of Clinical Trials (jRCT1040250129). Registration date: November 21, 2025.

**Supplementary Information:**

The online version contains supplementary material available at 10.1186/s12893-026-03528-5.

## Background

Midline laparotomy has remained a workhorse incision from the open era through the widespread adoption of laparoscopy and robotics because it enables rapid entry to the peritoneal cavity while minimizing injury to abdominal wall nerves, vessels, and muscle. Nevertheless, incisional hernia (IH) is the most common complication of midline incisions, with reported incidences of approximately 10–20% [1–5]. Rates are even higher—around 30–35%—in high-risk groups such as patients with obesity or abdominal aortic aneurysm [6–8]. IH causes pain, functional limitations, and reduced quality of life and may lead to serious complications including bowel obstruction and strangulation [5]. The public health burden is substantial: in the United States an estimated 348,000 IH repairs are performed annually, with related costs approaching 3.2 billion USD [9, 10]. Preventing IH is therefore a priority in abdominal surgery.

Currently, the most widely practiced suturing methods for midline laparotomy closure are interrupted suturing (IS) and continuous suturing. IS provides multiple anchoring points by closing the abdominal wall stitch by stitch, offering greater stability and reducing the risk of loss of fascial integrity. However, compared with continuous suturing, it requires more time and makes it difficult to achieve uniform tension at each knot. In contrast, continuous suturing allows faster closure with more even distribution of tension but carries disadvantages such as the risk of tissue ischemia due to excessive tightening and the possibility of wound failure if the suture unravels at a single point. Barbed sutures have been developed as novel materials designed to overcome these disadvantages.

Over the past several decades, suture strategies for closing midline laparotomy have been rigorously evaluated. Meta-analytic data suggest that continuous suturing with monofilament (non-barbed) sutures reduces IH compared with IS [5, 11]. In emergency settings such as fecal peritonitis and other contaminated abdominal procedures, a prospective multicenter randomized trial demonstrated that fascial closure with triclosan-coated barbed sutures reduced the rate of wound dehiscence (evisceration) compared with standard loop closure techniques [12].

Since Jacobs et al. first reported laparoscopic colectomy in 1991, minimally invasive surgery with a small abdominal incision has gradually become the standard approach for colorectal cancer in the 2000s [13]. Weber et al. first reported telerobotic-assisted laparoscopic right and sigmoid colectomies for benign disease in the early 2000s [14]. Soon thereafter, Hashizume and Tsugawa described three colonic resections for malignant disease performed with a robotic system [15, 16]. In Japan, robotic surgery has been reimbursed under the national health insurance system since 2018 for rectal cancer and since 2022 for colon cancer, and its utilization has shown a steady annual increase. In laparoscopic and robotic surgery, the midline incision is smaller than in open surgery, and several reports have suggested that the incidence of IH is therefore lower compared with open procedures [17, 18]. As minimally invasive approaches have reduced incision size, IH rates after laparoscopic surgery appear lower than in the open era; even so, IH after laparoscopic midline extraction closed with IS has been reported in the range of 5–13% [17, 19–21]. Pyo et al. reported an IH rate of 1.3% (1 out of 80 patients) at 12 months following abdominal fascial closure using a monofilament polydioxanone barbed suture (MONOFIX^®^) in their prospective single-arm clinical trial [22]. In addition, recent experimental and clinical studies have provided further insight into the contemporary use of barbed sutures. Experimental data suggest that the material properties of barbed sutures may contribute to stable tissue approximation and maintenance of tensile integrity during the healing process, and recent multicenter clinical data indicate that barbed sutures do not increase the risk of abdominal wall dehiscence compared with conventional sutures after laparotomy [23, 24]. These recent findings reflect a growing shift in fascial closure strategies in the era of minimally invasive and robotic colorectal surgery, highlighting the increasing clinical relevance of barbed sutures in contemporary practice.

IH following midline laparotomy has long been a focus of surgical research. While considerable knowledge exists regarding patient-related risk factors and the role of suture materials, technical aspects—particularly the influence of suture technique—have been less extensively evaluated [5, 11, 25]. Current evidence from randomized trials and meta-analyses indicates that mass closure using continuous suturing provides the most effective method for preventing IH in midline incisions. Compared with layered closure with IS, this approach is both technically simpler and faster to perform [25, 26]. In addition, the use of slow absorbable sutures rather than non-absorbable materials has been associated with lower rates of IH, reduced postoperative pain, and fewer wound infections [11, 25, 27].

The optimal, generalizable closure technique for contemporary small midline incisions, particularly in the setting of laparoscopic and robotic colorectal surgery—remains unsettled. To our knowledge, there has been no multicenter randomized controlled trial (RCT) directly comparing continuous suturing and IS techniques for midline mini-laparotomy closure in the setting of laparoscopic or robotic colorectal surgery. Given the persistent burden of IH and the suggestive but heterogeneous evidence favoring continuous barbed suturing (CBS), further protocolized evaluation is warranted.

Given the lack of high-quality evidence, we designed a multicenter randomized controlled trial to address this issue. This study aims to determine whether CBS is superior to IS in the setting of laparoscopic and robotic surgery. To our knowledge, this will be the first randomized controlled trial to evaluate the use of CBS in this context, and its findings are expected to make a significant contribution to the advancement of global surgical practice.

## Current status of midline mini-laparotomy closure in Japan (based on our original survey)

In Japan, fascial closure of midline incisions has traditionally been performed using IS, which has long been regarded as the standard method for midline fascial closure. In our nationwide survey conducted in 2024 across 50 institutions, 3 institutions (6%) reported using continuous suturing, 45 institutions (90%) used IS, and 2 institutions (4%) reported using both techniques. The survey also revealed that, in cases where IS was applied, more than half of the institutions (58%) responded that the knot tying was performed by surgeons with less than three years of surgical experience. This suggests that the involvement of relatively inexperienced surgeons in knot tying may contribute to the occurrence of IH through loosening of knots in IS.

Although several retrospective studies from Japan have examined the incidence of IH after laparoscopic colorectal surgery, none have directly compared continuous and IS for fascial closure. Consequently, the evidence base remains limited [19, 21]. As a result, continuous suturing has not yet been widely adopted in Japan in the context of laparoscopic or robotic colorectal surgery.

At Nagoya City University, midline incisions in colorectal surgery are closed using continuous suturing with STRATAFIX Symmetric PDS Plus, a barbed suture. STRATAFIX Symmetric PDS Plus, manufactured by Ethicon (Johnson & Johnson, Raritan, NJ, USA), is a barbed suture that does not require knot tying. By incorporating anchoring points to prevent loosening and eliminating the need for continuous traction, it addresses the main drawback of conventional continuous suturing—loss of tension along the suture line—which can lead to the development of IH. In our institution, among 215 cases performed between June 2022 and December 2023, the incidence of IH at one year postoperatively was 3.5%.

## Objective

The objective of the HIBISCUS trial is to compare CBS with IS performed using a monofilament suture. The overall aim of this study is to reduce the incidence of IH, which is one of the most common complications after abdominal surgery. We hypothesize that CBS will significantly decrease the rate of IH, thereby reducing patient morbidity, improving quality of life, and substantially lowering healthcare costs.

The primary endpoint is the incidence of IH within 18 months after surgery, primarily assessed using scheduled abdominal CT imaging performed at predefined follow-up time points in all patients, with clinical examination serving as a complementary assessment. Secondary endpoints include fascial closure time, postoperative complications (particularly SSI), postoperative wound pain, and the rate of reoperation or readmission.

## Methods/design

### Trial design

The HIBISCUS trial is designed as a prospective, multicenter, open-label RCT comparing CBS with IS.

The HIBISCUS trial is a multicenter, prospective, open-label, randomized controlled study comparing continuous barbed suturing with interrupted monofilament suturing for fascial closure of mini-laparotomy incisions (Fig. 1). The study is conducted across six participating institutions in Aichi Prefecture, Japan. Eligible adults with colorectal cancer undergoing elective laparoscopic or robot-assisted resection will be randomized in a 1:1 ratio to continuous closure using a barbed absorbable suture (STRATAFIX Symmetric PDS Plus; bite width of 5 mm and stitch spacing of 5 mm) or interrupted closure using a monofilament absorbable suture (PDS Plus; bite width of 8 mm and stitch spacing of 8 mm). This study is registered in the Japan Registry of Clinical Trials (jRCT1040250129). Registration date: November 21, 2025. Ethical approval was obtained from the Certified Review Board of Nagoya City University, and the protocol has been reviewed and approved by the institutional review boards of all participating hospitals. Patients will be recruited from six hospitals in Aichi Prefecture. The planned enrollment period is 1.5 years, followed by a 1.5-year follow-up period, resulting in a total maximum follow-up duration of 3 years. The study protocol was developed in accordance with the Standard Protocol Items: Recommendations for Interventional Trials (SPIRIT) 2013 guidelines.

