### Outcome parameters

#### Primary outcome

The primary endpoint is the incidence of IH within 18 months after surgery, primarily assessed using scheduled abdominal CT imaging performed at predefined follow-up time points in all patients, with clinical examination serving as a complementary assessment.

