### Evaluation of incisional hernia by abdominal CT

Two specialists (one radiologist and one gastrointestinal surgeon) at Nagoya City University will independently and blindly evaluate the CT images. In the event of disagreement between the two evaluators, a third specialist will adjudicate and make the final determination.

To avoid bias related to the suturing method, the evaluators will be blinded to treatment allocation, and allocation information will not be accessible to them.

IH will be assessed using the following parameters:

Presence or absence of IH (based on the EHS definition)Size of the fascial defectType of hernia contents

The assessment criteria will follow the definition proposed by the European Hernia Society (EHS), which defines hernia as “any abdominal wall gap with or without a bulge in the area of a postoperative scar, perceptible or palpable by clinical examination or imaging” [30]. The study’s calendars are shown in Table 1.

**Table 1 Tab1:** Study calendar of the HIBISCUS study

Time point	Enrollment	Allocation	Post-allocation					
			Surgery	POD 30	3 months	6 months	1 year	1.5 years
Informed consent	●							
Eligibility screen	●							
Patient background	●							
Blood test	●			●	●	●	●	●
CT	●					●	●	●
Colonoscopy							●※	
Allocation		●						
Surgery			●					
Surgical outcome			●					
Intraoperative adverse event			●					
Physical examination	●			●	●	●	●	●
Pathological findings				●				
Early complications				●				
Readmission				●	●	●	●	●
Adjuvant therapy					●	●	●	
Late complications					●	●	●	●
Survival						●	●	●
Resurrence						●	●	●

※Colonoscopy is generally performed 1 year postoperatively, but may be advanced to 6 months if complete evaluation was not possible due to preoperative bowel obstruction

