### Statistical analysis

Continuous variables will be summarized as mean ± standard deviation (SD) if approximately normally distributed, and as median with interquartile range otherwise; categorical variables will be presented as counts and percentages. Baseline characteristics will be evaluated descriptively without formal hypothesis testing, in accordance with standard recommendations for randomized controlled trials, which discourage statistical testing of baseline variables. All analyses will be performed according to the intention-to-treat (ITT) principle.

For comparisons between groups, t-tests or Mann–Whitney U tests will be applied to continuous variables depending on the distribution assessed using the Kolmogorov–Smirnov test with Lilliefors correction. Categorical variables will be compared using chi-square tests or Fisher’s exact tests, as appropriate.

The primary endpoint of this RCT is the incidence proportion of IH at the mini-laparotomy site. Differences between groups will be evaluated using a two-sided chi-square test for proportions with a two-sided significance level of 5%, based on the prespecified hypothesis that CBS reduces the risk of IH compared with IS. The primary analysis population will include all randomized participants according to the ITT principle. A per-protocol set (PPS) analysis will be conducted as a sensitivity analysis including those who complete the allocated intervention according to the protocol.

Secondary endpoints—including intraoperative outcomes, early postoperative outcomes, the incidence of intraoperative complications, and readmission within 90 days after surgery—will be summarized descriptively for each group.

For the primary endpoint analysis, the incidence proportion of IH during the follow-up period and the corresponding 95% confidence intervals will be calculated for each group. In addition, the odds ratio and 95% confidence interval for IH incidence in the CBS group relative to the IS group will be estimated.

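### Masking covers only the CT readers; patients could be kept unaware of their closure with little effort, which would protect wound pain from expectation bias

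*Protocol article*

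**What the plan says.** The Trial design section describes the trial as "designed as a prospective, multicenter, open-label RCT comparing CBS with IS"; the Abstract also calls it open-label. The article gives no reason for leaving patients unmasked and describes no step to keep the arm from them.

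Masking appears in one place, the section on evaluating incisional hernia by CT. Two specialists "will independently and blindly evaluate the CT images", a third settles disagreements, and "the evaluators will be blinded to treatment allocation, and allocation information will not be accessible to them". The Primary outcome section rests the endpoint mainly on scheduled CT, "with clinical examination serving as a complementary assessment".

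The Objective lists among the secondary endpoints "postoperative wound pain, and the rate of reoperation or readmission". Under Postoperative data, use of analgesics after postoperative day 5 is an item to be recorded; it is not listed as an endpoint. The Statistical analysis section says that secondary endpoints "will be summarized descriptively for each group".

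**The concern.** Pain is a subjective outcome. If patients know which closure they received, and staff who know it talk to them about it, a difference in reported pain mixes the effect of the closure with the effect of knowing. Complaints of pain can also lead to analgesic requests and to readmission, so those are exposed at one remove. Masking the CT readers does nothing for any of these.

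The surgeon cannot be masked to a suturing technique, but that does not mean the patient must know it. The plan already accepts the principle for imaging: "To avoid bias related to the suturing method, the evaluators will be blinded to treatment allocation". It does not carry that reasoning over to the outcome most open to expectation. The Discussion names learning-curve effects, differences between centers and suture caliber as limitations, but not the lack of patient masking.

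**Working it through.** The claim itself needs no arithmetic. The steps set the relevant sections side by side.

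**1. Who is masked.** CT readers: yes (CT evaluation section). Patients: not described, under an open-label label (Abstract, Trial design). Clinical examiners at outpatient visits: not stated. Operating team: necessarily aware.

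**2. What differs between the arms.** The comparison is of continuous barbed against "interrupted monofilament suturing for fascial closure of mini-laparotomy incisions". The Interventions section gives the differences: suture product, caliber (size 1 against size 0), bite width and spacing (5 mm against 8 mm), and continuous against interrupted placement. All lie in the fascial layer.

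**3. What the patient sees or does.** The outpatient visits, the CT scans at 6, 12 and 18 months and the study calendar are the same for both arms. Allocation is generated in REDCap, so the patient need not be told. No section asks one arm to do anything different after surgery. I assume that skin closure does not differ by arm; the article does not describe it.

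**4. What each outcome depends on.**

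| Outcome | Status in the plan | Exposure to patient expectation |
|---|---|---|
| Hernia by CT reading | main basis of the primary endpoint | none in the masked reading |
| Wound pain | secondary endpoint | direct |
| Readmission | secondary endpoint | indirect, through complaints and clinicians' decisions |
| Analgesics after day 5 | recorded item, not an endpoint | indirect, through requests and prescribing |

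**5. What the bias does to the estimate.** Let δ be the true difference in pain and b the difference caused by knowing the arm. The expected observed difference is δ + b. Nothing recorded in the trial separates the two, and b does not shrink as the sample grows. This holds whether the difference is tested or only described.

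**6. What cannot be computed.** The article gives no pain instrument, time points, rater or variability, and nothing from which b could be estimated. An article may leave such details to the full protocol, so their absence is not a finding, but it means that no size can be put on the bias.

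**7. Effect of masking on the sample size.** None. The plan's figure rests on the primary endpoint alone and reproduces. With 11.5% against 3.9%, mean 7.7%, two-sided 5% and 80% power:

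n = [1.960·√(2·0.077·0.923) + 0.842·√(0.115·0.885 + 0.039·0.961)]² / (0.115 − 0.039)² = (0.739 + 0.314)² / 0.005776 ≈ 192 per group.

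No input to this formula depends on whether patients are masked.

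**The case against.** The strongest reply is that this is a design preference with no effect on the main conclusion. The primary endpoint rests mainly on CT scheduled for all patients and read by masked specialists, so what patients believe does not drive the reading. That stands, and it limits the point to secondary outcomes. A reader might take open-label to mean that nothing is masked; the CT section rules that out.

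Second, the mechanism is partly assumed. The consent text is not shown, so a reader who infers that patients are told a newer and better suture is on trial goes beyond the documents. The stated hypothesis concerns hernia, with morbidity, quality of life and cost as consequences; it does not promise less wound pain. The direction of any bias is therefore unknown. That pain is self-reported is also an inference. What remains is that pain is subjective and patients are not masked.

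Third, it is tempting to assume a shift in pain scores and compute the chance of a falsely significant difference. The documents do not support that. Any such shift would be invented, and a formal pain test is not clearly planned. The Statistical analysis section has a general sentence on t-tests and Mann–Whitney tests, but it does not name pain, and the sentence on secondary endpoints says they are described. Describing a biased difference does not remove the bias, however.

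Fourth, masking is not free, and no section discusses its feasibility. Ward and clinic staff would have to withhold the arm over 18 months of visits, and some patients would learn it. Readmission also involves clinicians who may know the arm, so patient masking protects it only in part. Masking patients also leaves open whether the clinical examiners are masked, on which the article is silent. These points reduce the gain but do not cancel it for wound pain.

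**Conclusion.** The point holds in a limited form. The plan fixes the trial as open-label and masks only the CT readers, although the arms differ in a layer the patient cannot see and follow-up is common to both. Wound pain is therefore open to expectation bias, with readmission and analgesic use exposed less directly. The masked CT reading that mainly determines the primary endpoint is not affected.

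The bias has no size that can be derived from the documents, and no false-positive rate should be attached to it. The conclusion rests on three assumptions: pain is rated by, or depends on, the patient; skin closure and aftercare do not reveal the arm; and staff can reasonably withhold the allocation. If these hold, patient masking is an inexpensive improvement to a secondary comparison. It is not a repair of the primary analysis.

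**What to change.** - In the Trial design section and the Abstract, replace the open-label description with patient-masked, with masked CT readers and an unmasked operating team.
- State in the consent that the closure used is not disclosed to the patient until after the 18-month assessment.
- Keep the arm off the discharge summary and other patient-facing documents.
- Record wound pain by patient self-report.

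The cost is a change to consent and procedure wording. It needs no added staff or procedures and no change to the sample size or visit schedule. The downside is that staff must withhold the arm and some patients may still learn it.

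If the sponsor judges masking infeasible, the plan should give the reason and name the lack of patient masking as a limitation for wound pain, beside those already listed in the Discussion.
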